## 1. Introduction

The World Health Organization’s (WHO) Framework Convention on Tobacco Control (FCTC) suggests a number of measures to reduce the demand for and supply of tobacco. Elimination of all forms of illicit tobacco trade (Article 15) is an essential tobacco control measure [1,2]. Illicit trade may include large- and small-scale smuggling, illicit manufacturing, and counterfeiting of existing brands [1]. Cigarettes are a particularly attractive product to smugglers [2]. As cigarettes in Low- and Middle-Income Counties (LMICs) have relatively higher taxes compared to other tobacco products such as birris and smokeless tobacco [3], evading tax by diverting cigarettes into the illicit market (where sales are largely tax-free) can generate a considerable profit margin for smugglers [2,4]. Illicit trade undermines the effectiveness of tobacco tax policies, results in availability of cheap cigarettes to smokers, and thus increases tobacco use and tobacco related deaths [2,3]. Elimination or curbing illicit trade will therefore increase price and tax revenue to governments and reduce tobacco consumption and tobacco-related premature deaths [3,5].

The share of illicit in total cigarette consumption is estimated to be 11.6% globally and 16.8% in LMICs [2]. Tobacco companies claim that illicit trade in cigarettes has been growing rapidly since the 1990s [4], and often use inflated estimates of illicit cigarettes to argue against cigarette tax increases [5,6,7,8]. In the absence of national-level independent data on the extent of illicit cigarette trade and limited data on cigarette confiscation provided by the enforcement authorities [3,9], tobacco companies manipulate evidence to their advantage and use these tactics to continually lobby governments for reducing cigarette taxes [3,6,7].

In Bangladesh, 35.3% of adults (38 million) use tobacco regularly, 14% (15 million) use cigarette, and 5% (5.3 million) use “birri” [10]. However, there has been no independent published evidence measuring the extent of illicit tobacco trade in Bangladesh. Nevertheless, following industry estimates, it has been claimed that the illicit cigarette trade would be about 2% of the total cigarette market, leading to a revenue loss of 8 billion Taka, 4% of the total tobacco revenue [11]. 

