## 2. Materials and Methods 

Measuring illicit tobacco trade is a complex task due to the illegal nature of the activities involved [2]. Various methods have been used to assess the extent of illicit trade, such as measuring the difference between consumption and tax paid sales, interviewing smokers, studying features of cigarette packs and econometric modeling, each having their own strengths and weaknesses [3,4,12,13]. We will use observational methods and collect data from empty cigarette packs from three sources: (a) from the retailers resulting from their loose cigarette sale [3,14]; (b) littered packs from the streets surrounding the retailers [3,15,16]; and (c) littered packs from trash recycle market. The last one can be considered as an innovation in the methodology for not being applied before and could be particularly useful in LMICs where trash recycle markets are established. Regardless of the pack source, such observational studies provide a direct way to assess illicit trade [7,17].

Once collected, we will examine certain characteristics of cigarette packs such as “no mention of retail price”, “mention of brand element”, “no graphic and textual health warnings”, “no declaration”, “a duty-free sign”, and “absence of correct and authentic tax stamps” of cigarette packs as indicators of being illicit [12]. Such information could also be collected either directly from tobacco users and/or by inspecting tobacco users’ packs. However, as “loose selling” of cigarettes is common and permitted by law in Bangladesh, consumer surveys and pack inspections are of limited use. On the other hand, loose selling makes retailer pack collections more relevant. We will therefore adopt the approach developed by John and Ross (2018) [3] to measure the extent of illicit cigarette sold as retail in Bangladesh. In addition, a structured questionnaire will be used to collect information from retailers selling cigarettes.

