## 3. Analysis Plan

We will classify a cigarette pack as illicit if it has at least one of the following attributes: No mention of “retail price”: It is mandatory to print the retail price of the goods “on the body of the goods or on every package, sachets or cells distinctly, conspicuously and indelibly”. This applies to cigarettes, and packs not containing the retail price can be considered illegal [21].Mention of brand element: Packets should not contain any brand elements, for instance Light, Mild, Low Tar, Extra, and Ultra. Packs mentioning brand element will be considered illegal [22].No graphic health warnings: Health warnings shall be printed on both sides of the packet covering at least 50% of the total area of each main display area. In addition, the warnings should be in colored pictures. Rules notified further suggests that the ratio and written warnings should be 6:1 and the written warnings has to be printed in black background with white font color. Packs not fully complying the above rules will be considered illegal [21,22].No textual health warnings: The following warnings should be printed on the packet in Bengali, otherwise it can be considered as illegal [21,22].
(a)Smoking causes throat and lung cancer;(b)Smoking causes respiratory problems;(c)Smoking causes stroke;(d)Smoking causes heart disease;(e)Second-hand smoke causes harms to the fetus;(f)Smoking causes harms to the fetus; or(g)Second-hand smoking causes death.No declaration: Selling of tobacco products without having the statement “Sales allowed only in Bangladesh” printed on the packets would be illegal [22].A duty-free sign: Cigarette packs collected from retailers with a “duty-free” sign will be classified as illegal as these are to be sold in Duty Free shops only and should not be available in the market.Absence of correct and authentic tax stamp/banderole: The government has made it obligatory to use tax stamp or banderole on cigarette packets. Any sale of cigarette without this tax stamp or banderole is legally prohibited. The banderole/stamp of cigarette pack of different size and design had been defined [21]. We will check if the packs have used banderole/stamp correctly as per the SRO and VAT Booklet, and if the banderole/stamp is genuine.

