In general, all pack characteristics considered for detecting legitimacy in the retailer sample might also be accepted for those in littered or trash samples. Nevertheless, one of the limitations of the above general approach is that it might fail to distinguish between tax evasion and avoidance. More specifically, there may be some legally purchased duty-free packs as well as those bought from neighboring countries, in a sample from street, while also having illegally purchased and illegally sold packs in the retail shops belonging to that street. This possibility might result in under- or overestimation of the illicit cigarette trade. Hence, it rationalizes the application of an adjustment factor while measuring the magnitude of illicit cigarette in the sample collected particularly from street and trash recycle market. Table 3 exemplifies a thematic presentation of legitimacy criterion of a cigarette pack and adjustment requirement in the estimation. 

Assuming that the littered packs in the streets would by and large reflect the average characteristics of those sold by different retailers on the same street, the following adjustment method would be applied:

Suppose DF_L_ is the proportion of duty-free packs (both legal and illegal) in the littered sample and DF_R_ is the proportion of duty-free packs (all illegal) in retailer sample. Then, the estimated proportion of illegal duty-free packs from littered sample would be
=DF_R_ if DF_L_ > DF_R_; and
=DF_L_ if DF_L_ ≤ DF_R_.   

Similar adjustment process would be followed while estimating extent of illicit cigarette using packs from trash recycle sample. It should be noted here that self-made cigarette using tax-paid tobacco powder or crushed tobacco may not be the scope of current work. However, a pack for a local category of cheap cigarette known as “birri” would be collected and examined for its compliance as per the study definition. Statistical Analysis (STATA) software version 15 would be used. The main statistical analysis will report the frequencies and proportions of cigarette packs that do not comply with the tobacco control laws and falls within the study definition of illicit. 

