This study is being conducted as part of a research consortium of fifteen partner organizations across eight countries (Bangladesh, Ethiopia, Ghana, India, South Africa, the Gambia, Uganda, and the UK) funded by the Global Challenges Research Fund in the UK and named the “Tobacco Control Capacity Programme” [39]. We have established a national stakeholders’ group in Bangladesh and arranged several stakeholder engagement meetings to get their feedback on the study protocol. 

The successful implementation of the protocol is subject to endorsed inspection of collected packs and data recording about the authenticity of tax stamp. According to the local tobacco control laws, a tax paid pack must contain the tax stamp and we are in need of examining the security features of the tax stamp for study purpose. In practice, in most cases, these tax stamps are affixed in the upper left- or right-hand corner in the outer part of a cigarette pack. Thus, it might happen that the required tax stamp is removed, lost, or torn while opening by the retailers or littering by the smokers into the streets and trash bins. Considering this potential threat, the gold standard would have been collecting the unopened packs for tax and other compliance inspection [12]. This scope is limited in the current context due to the fund challenge that has to be made with respect to the sampling design. Hence, training on eligibility criterion for an empty cigarette pack to be included in the inspection basket would be of sheer importance. All the packs where tax stamps are not in proper status to be checked for authenticity would be excluded from the study. 

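### Excluding packs whose tax stamp cannot be checked selects on part of the definition of illicit, and can bias the headline proportion, probably downward

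*Protocol article*

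**What the plan says.** The protocol article, section 3 (Analysis Plan), sets the rule: "We will classify a cigarette pack as illicit if it has at least one of the following attributes". Seven attributes follow. Six concern retail price, brand elements, graphic warnings, textual warnings, the declaration of sale in Bangladesh, and a duty-free sign. The seventh is the stamp: "Absence of correct and authentic tax stamp/banderole: The government has made it obligatory to use tax stamp or banderole on cigarette packets". The text goes on: "Any sale of cigarette without this tax stamp or banderole is legally prohibited". Section 2 lists the same indicator, "absence of correct and authentic tax stamps". The headline result is built on this definition: "The main statistical analysis will report the frequencies and proportions of cigarette packs that do not comply with the tobacco control laws".

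Section 4 (Discussion) observes that on an empty pack "it might happen that the required tax stamp is removed, lost, or torn while opening by the retailers or littering by the smokers". It names unopened packs as the gold standard, says funding rules them out, and concludes: "All the packs where tax stamps are not in proper status to be checked for authenticity would be excluded from the study". It makes no exception for packs with no trace of a stamp, or for packs that can be classified on another criterion.

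**The concern.** Whether a pack stays in the study depends on its stamp, and the stamp is one of the attributes that define the outcome. Exclusion is therefore unlikely to be independent of illicit status. On an empty pack, no stated rule separates a stamp never affixed from one lost at opening. The sentence removes both.

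Three parts of the study are affected.

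- **Question (a).** The headline proportion is taken over packs selected on a component of the outcome.
- **Question (b).** Section 4 says a tax-paid pack must carry the stamp, so an unstamped pack is the plainest sign of unpaid tax. The rule removes it from the description of evasion.
- **Question (c).** Retailer, street and trash packs may lose stamps at different rates. A difference between sources could then reflect exclusion, and agreement could reflect a shared bias. Section 4 relies on the three-source comparison for validity, but the exclusion applies to all three sources, so the comparison does not cure it.

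The study is meant to test industry claims, and the article reports that "it has been claimed that the illicit cigarette trade would be about 2% of the total cigarette market". Against a figure that small, a modest selective loss can matter.

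**Working it through.** The article gives no rate of stamp loss or exclusion, so there is no planned figure to reproduce. The rates below are assumptions.

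**Step 1. Apply both rules to the same packs.**

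| Pack | Section 3 | Section 4 |
|---|---|---|
| Genuine stamp intact, otherwise compliant | licit | kept |
| Never stamped | illicit | nothing to check: excluded |
| Tax paid and compliant, stamp lost at opening | no stamp to show, though truly licit | excluded |
| Retailer pack, stamp uncheckable, no retail price | illicit on price alone | excluded |

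The second and fourth rows show the conflict.

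**Step 2. Effect on the proportion.** Let p be the true illicit share, and e and f the exclusion rates among illicit and licit packs. The reported share is

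R = p(1−e) / [p(1−e) + (1−p)(1−f)].

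Exclusion multiplies the illicit odds by (1−e)/(1−f). So R < p if e > f, R = p if e = f, and R > p if e < f.

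**Step 3. Equal stamp loss.** Let s be the share of illicit packs that never carried a stamp, and L the share of stamped packs whose stamp is lost or torn, equal in both groups. Assume all licit packs were stamped. Then e = 1−(1−s)(1−L) and f = L. L cancels, leaving R = p(1−s)/(1−ps). The values of p are the shares quoted in section 1, used only as scenarios.

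| True p | s = 0 | s = 0.25 | s = 0.5 | s = 0.9 |
|---|---|---|---|---|
| 2% | 2% | 1.51% | 1.01% | 0.20% |
| 11.6% | 11.6% | 8.96% | 6.16% | 1.30% |
| 16.8% | 16.8% | 13.15% | 9.17% | 1.98% |

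Example: p = 0.168 and s = 0.5 give 0.084/0.916 = 9.17%.

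**Step 4. Unequal stamp loss.** Take p = 16.8% and s = 0.25.

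- Loss of 5% in stamped illicit and 40% in licit packs: 0.168×0.75×0.95 = 0.1197 and 0.832×0.60 = 0.4992, so R = 0.1197/0.6189 = 19.3%.
- Rates swapped: 0.168×0.75×0.60 = 0.0756 and 0.832×0.95 = 0.7904, so R = 0.0756/0.8660 = 8.7%.

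The first case overstates the share. There e = 1−0.75×0.95 = 0.2875, which is below f = 0.40.

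**Step 5. The opposite rule.** If every missing stamp counts as illicit, the share reads p + (1−p)L. With p = 5% and L = 20% this is 0.05 + 0.95×0.20 = 24%. With p = 2% it is 0.02 + 0.98×0.20 = 21.6%.

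**The case against.** **The rule has a sound purpose.** Empty packs lose stamps, the article says so openly, and step 5 shows that treating lost stamps as evasion would badly inflate the result. This stands, and it rules out simply reversing the rule.

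**The sentence may cover only damaged stamps.** A stamp not fit to be checked can mean one that is present but torn, in which case a never-stamped pack would stay in and count as illicit. This reading is possible. However, the article does not state it, and the lines just before name removed and lost stamps too. Even the narrow reading would discard packs with a torn stamp that fail another criterion.

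**A reader might infer that the estimate must be too low.** The documents do not support that. The direction depends on e and f, for which no rates are given. The definition is also broad: Table 3 makes a tax-paid, non-compliant retailer pack illegal, and such a pack would ordinarily carry a stamp. If these form most of the illicit packs, e approaches f and the bias shrinks. If licit packs are excluded more often, it reverses.

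**A reader might also infer that any pack failing another criterion is illicit whatever its source.** For retailer packs that follows from section 3. For street and trash packs it does not. Section 3 recognises legally bought duty-free and neighbouring-country packs there, and Table 3 calls non-compliant packs from these sources possibly legal or illegal and applies an adjustment.

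**Distortion of question (c) is plausible, not shown.** The article names opening and littering as causes of loss but gives no rates by source.

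**Conclusion.** The concern holds in a conditional form. As written, the exclusion in section 4 conflicts with the stamp criterion in sections 2 and 3, and it selects on a component of the outcome. Section 4 discusses other selection threats but not this one, and expects none to remain.

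Downward bias is likely where many illicit packs never carried the stamp, and certain under the equal-loss model of step 3 whenever s is above zero. With half never stamped, the reported share is roughly half the true one. The size in this study is unknown because it rests on assumed s and L. It could be close to zero, and the sign could reverse under unequal loss. What does not depend on those assumptions is that the rule discards classifiable packs and leaves the treatment of never-stamped packs in conflict.

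**What to change.** Replace the exclusion sentence in section 4 with a rule along these lines.

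1. Keep every collected pack. Code its stamp as authentic, present but not authentic, torn with remnant, or no trace.
2. Classify each pack first on the six non-stamp criteria. A retailer pack that fails one is illicit whatever its stamp. For street and trash packs, the result stays subject to the adjustment in section 3 and Table 3.
3. For packs otherwise compliant but with an indeterminate stamp, report a lower bound (all licit) and an upper bound (all illicit), both over all retained packs.
4. Report the figure from checkable stamps only as a separate sensitivity result. It need not lie within the bounds. For example, with p = 10%, e = 80% and f = 20% it is 0.02/0.74 = 2.7%, while the lower bound is 10% if every excluded illicit pack fails another criterion.
5. Tabulate the indeterminate share by source, so that the comparison for question (c) can be read against it.

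The cost is small. Section 2.2.5 already brings the packs to the research office for inspection and coding, so this adds one coded field and a change of wording. The drawback is that the result becomes a range, which may be wide if many stamps are lost.

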### 2.1. Study Sites and Sampling Design

Bangladesh is divided into eight administrative divisions (highest administrative unit) and 64 districts. Bangladesh also has large international land borders with neighboring countries, and therefore 31 districts in six divisions border with India and Myanmar (Table 1). In Appendix A, Figure A1 presents the map of Bangladesh where the green colored places represent the two divisions with no land border area and the rest share land borders with neighboring countries. 

We will use post codes as the primary sampling unit (PSU) and select PSUs using a multi-stage random sampling technique [14]. In a division having districts with borders, we will only consider those districts having borders for inclusion in the study, and randomly select one such district from the division. For instance, while considering Rajshahi division, among eight districts, four (namely, Naogaon, Rajshahi, Nwabganj, and Joypurhat) have areas with a land border. Therefore, the sampling frame would consist of those four districts only and one will be randomly selected. In two divisions, Dhaka and Barisal—where there is no district with international land border—we will randomly select one district from each. For example, in Barishal division, there are six districts (namely, Bhola, Barishal, Barguna, Pirojpur, Patuakhali, and Jhalokathi) and none of them have international border, hence all of them would be considered in the sampling frame for the purpose of random selection. Hence, eight districts will be selected, one from each division. 

Within a district, we will select 10 post codes randomly, 60 post codes from border and 20 from non-boarder districts—a total of 80 post codes from eight districts. The PSUs in each district will also be stratified by rural (five post codes) and urban (five post codes) to ensure maximum geographical variation. Post codes (PSUs) under city corporation or paurasava (municipality) will be defined as “urban” while postcodes outside of those places will be considered as rural. Currently, there are 1216 post codes, each with an average area of 121 square kilometers. The list of the post codes is available by districts and sub districts [18]. Table 2 illustrates the sampling design. 

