#### 2.2.1. Collecting Packs from Tobacco Retailers

The data collection team will determine a central point (such as a bus station, a government building, or a market place) in each PSU. All types of shops, such as tea stalls, kiosks, supermarkets, department stores, and cigarette shops that sell cigarettes or birri, or both, would be eligible to take part in the study. Enumerators will walk half a kilometer in both directions on the main street around the public gathering place and approach all the retailers meeting the eligibility criteria. All eligible retailers will be provided with both verbal and written information about the study. If they agree to take part, they will be required to sign the consent form. Following consent, the field worker will proceed to pack collection. The retailers would be supplied with a “collection bag” on the previous day and asked to keep all the empty packs resulted from loose sale on the following day since the shop opened in that bag. All “collection bags” will be retrieved by the field workers at the end of the business day. We will provide a small monetary reward of BDT 3 (GBP 0.03) per empty pack deposited in the collection bag. In case the empty pack of the cheapest and popular brands were not available in the bag from a particular retailer, the team would take a picture and code all the relevant attributes of such pack observed in the shop itself [3]. 

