#### 2.2.2. Collecting Discarded Packs from Streets

In addition to collecting empty packs from the tobacco retailers, discarded packs from the streets where those retailers are established and also from some other locally important streets around public gathering places will be accumulated [3]. The distance that would be covered in each street would be one kilometer (half a kilometer in each direction). The field workers would use separate “collection bag” with unique identification number for collecting the discarded packs in each area. The pack collection from streets would take place simultaneously during the day when the “collection bag” to the retailers would be distributed. The street selection would also consider the street condition for walking and possibility of finding littered packs. Necessary safety equipment such as masks and gloves will be provided to the field staff while collecting littered packs. 

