#### 2.2.6. Ethical Considerations

The primary principles of good ethical practice such as autonomy, justice, beneficence, and non-maleficence will be maintained during the study. We are conscious that retailers could have concerns that the research may negatively impact their business, and interviewers could feel uncomfortable during the interaction with retailers. We will adopt multiple measures to mitigate these concerns. First, all potential retailers will be provided with information regarding the project and written consent will be taken prior to data collection. Those who do not agree to participate after reviewing the study information will not be enrolled in the study. The reasons for declining to participate in the study will be recorded. Second, retailers will be reassured that all information collected during the course of the study will be kept strictly confidential. Third, researchers will be trained on techniques for handling conflict, threats, abuse, or compromising situations. We will specifically train researchers to ask questions in a non-judgmental manner and not to put any pressure on the respondents, if they show signs of reluctance in answering one or more questions. Our data collection team will be respectful to the retailers and will avoid interference with the normal flow of business. Interviewers will only continue the interview when the retailer is not dealing or in the vicinity of customers. Every interviewer will have the right to decline collecting packs from a retailer in a location that makes him or her feel unsafe. 

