Another important potential limitation of the proposed methodology would be its ability of correct estimation for the size of illicit market. Since the unit of observation from where packs would be collected is retail cigarette shops, selection bias might remain present in the estimation. The estimate would be overestimated if pack collection takes place in an area where illegal tobacco products are known to be traded. In contrast, the estimates would be underestimated if retailers purposefully preserve the licit cigarette packs in the collection bag. Moreover, conditioning that illicit cigarettes are sold in full packs in general rather than single sticks, collecting empty packs from retailers might underestimate the magnitude. Considering all these potential threats, we expect the study would be free from selection bias as the retailer selection would be completely random covering the urban–rural and border–non-border perspective around the country. The validity and representativeness of the estimate measured using the packs collected from retailers would be ensured by comparing that with the estimate retrieved from littered packs from the streets and packs collected from the trash recycle market in the same neighborhood. Estimates from the two later sources to a greater extent would address the limitations if retailer deposit only licit packs or illegal cigarette happens to be sold in full pack. The comparison of results and further analysis of illicit packs from these three sources would help us to examine the existence of any systematic difference among them. Absence of systematic difference would ensure the possible unbiasedness of the estimates [12].

Finally, in the absence of any prevalence data at the division or district level, it would not be possible to propose a sample size weighted on the local smoking prevalence or smoking intensity. Bangladesh has completed two rounds of Global Adult Tobacco Survey (GATS). However, the first round does not have district level or divisional level information on smoking prevalence while the data from second round have not been released yet. 

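### The Discussion calls retailer selection completely random, but randomisation stops at the post code and the choice of retailers within it is purposive

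*Protocol article*

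**What the plan says.** Section 2.1 sets out the random part of the design: "We will use post codes as the primary sampling unit (PSU) and select PSUs using a multi-stage random sampling technique". One district is drawn per division, then ten post codes per district (five urban, five rural). Table 2 names simple random sampling for the post codes.

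Section 2.2.1 governs what happens inside a post code. First, "The data collection team will determine a central point (such as a bus station, a government building, or a market place) in each PSU". Then, "Enumerators will walk half a kilometer in both directions on the main street around the public gathering place and approach all the retailers" that are eligible. No random draw is described for the point, the street or the shop.

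Section 2.2.6 adds two filters on who takes part. On retailers: "Those who do not agree to participate after reviewing the study information will not be enrolled in the study". On field staff: "Every interviewer will have the right to decline collecting packs from a retailer in a location that makes him or her feel unsafe".

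The limitations paragraph in section 4 first admits that selection bias may persist and names threats in both directions. It then concludes that "we expect the study would be free from selection bias as the retailer selection would be completely random", with reference to urban–rural and border–non-border coverage. It relies on comparison with street and trash-market packs to secure validity and representativeness.

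**The concern.** The property claimed in section 4 is not a property of the procedure in section 2.2.1. A team-chosen central point followed by a take-all walk along one street is a purposive stage. A shop on a side street, or near another gathering point in the same post code, has no chance of entering the retailer sample.

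This bears on research question (a), the proportion of cigarettes sold at retail that are illicit. The result is meant to counter tobacco industry claims, and the only national figure in the document is an industry-based one of about 2%. At that level an error of one or two percentage points matters. A claim of randomness that the methods section does not bear out also gives critics an easy reason to dismiss the estimate.

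The claim is also asked to do too much. Even a truly random draw of retailers would not deal with two threats named in the same paragraph: retailers depositing only licit packs, and illicit cigarettes being sold as full packs.

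**Working it through.** **1. The random stages, reproduced.** Inputs from section 2.1: 8 districts, 10 post codes each, 6 border and 2 non-border divisions.
- 8 × 10 = 80 post codes; 6 × 10 = 60 border; 2 × 10 = 20 non-border; 8 × (5 + 5) = 80.

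These agree with the stated figures. The random part is internally consistent and ends at the post code.

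**2. Each selection step against the claim.**

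| Step | Where stated | How chosen |
|---|---|---|
| District | 2.1, Table 2 | Random, one per division |
| Post code | 2.1, Table 2 | Random, within urban and rural strata |
| Central point | 2.2.1 | Determined by the team |
| Street | 2.2.1 | Main street at that point, 0.5 km each way |
| Retailer | 2.2.1 | All eligible shops on that stretch |
| Participation | 2.2.6 | Consent, and interviewer safety |

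The sentence in section 4 concerns retailers, and none of the steps below the post code is random.

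**3. What the purposive stage can do to the estimate.** Let s be the share of a post code's retail cigarette sales made on the covered stretch, m the illicit share there and e the illicit share elsewhere.
- True share = s·m + (1 − s)·e
- Bias = m − true share = (1 − s)(m − e)

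The document gives no value for s, m or e. As an illustration, assume s from 10% to 50%, one illicit share at 2% (the industry-based level in section 1) and the other at 4% to 6%.
- m = 2%, e = 4%, s = 0.5: true share 0.5 × 2 + 0.5 × 4 = 3.0%; bias −1.0 point.
- m = 2%, e = 6%, s = 0.1: true share 0.1 × 2 + 0.9 × 6 = 5.6%; bias −3.6 points.
- m = 4%, e = 2%, s = 0.5: true share 0.5 × 4 + 0.5 × 2 = 3.0%; bias +1.0 point.
- m = 6%, e = 2%, s = 0.1: true share 0.1 × 6 + 0.9 × 2 = 2.4%; bias +3.6 points.

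The bias is zero when m = e, or when the stretch carries all sales (s = 1). The number of post codes does not appear in the formula, so adding post codes does not remove it.

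**4. Non-participation, a separate mechanism.** Suppose 30% of approached retailers refuse or are skipped, their illicit share is twice that of participants, and pack volume per retailer is equal (all assumed).
- Participants at 5%: 0.7 × 5 + 0.3 × 10 = 6.5%, against 5% observed.
- Participants at 2%: 0.7 × 2 + 0.3 × 4 = 2.6%, against 2% observed.

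This illustrates non-response only and says nothing about the choice of point and street.

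**5. Whether the cross-check covers the gap.** Under section 2.2.2, litter comes from the retailers' own streets and from other important streets near gathering places, and "The street selection would also consider the street condition for walking and possibility of finding littered packs". Under section 2.2.3, trash-market packs are included only if a market exists and packs can be obtained, and such markets are limited in rural areas. Section 4 places both sources in the same neighbourhood as the retailers. The comparison can reveal selective depositing or full-pack sales. It cannot reveal a difference between these places and the rest of the post code, because the sources largely share the location.

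**The case against.** The sentence is hedged as an expectation. It refers to coverage of urban, rural, border and non-border areas, where districts and post codes are in fact drawn at random. It sits in a paragraph that admits possible selection bias. Approaching every eligible shop on a fixed stretch removes enumerator discretion over individual shops and is no fault in itself. Consent and the right to leave an unsafe place are ordinary ethical provisions. The rule on litter streets concerns another pack source.

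Much of this stands, and it narrows the point. It does not rescue the claim: the sentence says that retailer selection is random, and no such draw is described.

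A reader might infer more than the document supports:
- **That the bias is mainly downward.** Section 2.2.1 lists market places among the possible central points, and section 4 itself names overestimation where illegal trade is known to occur. The direction is open.
- **That the study would report its estimate as unbiased.** Section 4 ties only possible unbiasedness to the absence of systematic difference among the three sources.
- **That 6.5% against 5% measures the defect.** Its inputs are all assumed and it models non-response, not the purposive stage.
- **That 1 km in an average post code of 121 square km measures coverage.** A length set against an area says nothing about the share of shops or sales reached, and the average is over all 1216 post codes.

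**Conclusion.** The point holds as a contradiction between section 4 and section 2.2.1. Retailer selection is random down to the post code and purposive within it, then filtered by consent and interviewer safety. Freedom from selection bias therefore cannot rest on randomness.

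The size and direction of any bias cannot be determined from the document. The range of 1.0 to 3.6 points in either direction depends wholly on the assumed sales and illicit shares, and shows only that the error could matter beside a claimed level of about 2%. Agreement among the three pack sources would be useful evidence on selective depositing and full-pack sales, but not on location.

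**What to change.** 1. **Wording.** Replace the phrases *completely random* and *free from selection bias* in section 4. State that selection is random to post code only and purposive within it. Limit the retail estimate to outlets on main streets near public gathering places. Add that agreement among the three sources does not establish absence of location bias. This costs nothing.
2. **Central point, where feasible.** Before the visit, list candidate central points in each of the 80 sampled post codes and draw one by random number. This removes team discretion for the price of a short listing task; the document mentions no existing list of such points. It still draws among gathering places, so it does not bring back-street shops into the sample, and the limitation in item 1 remains.
3. **Participation.** Report the numbers of eligible retailers, refusals and interviewer declines, alongside the refusal reasons that section 2.2.6 already records. Add a simple sensitivity range for non-participants. This needs a contact log.
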